**Special Notes on Efficacy Assessment 4.4.4**

When nodular lesions are included in the overall target lesion assessment, and the size of the lesion reduces to 'normal' size (< 10 mm), they will still have a lesion size scan report. To avoid overestimating the situation reflected by the increase in lesion size, even if the lesion is normal, the measurement results will still be recorded. As previously mentioned, this means that subjects with a complete response will not be recorded as 0 on the CRF.

If efficacy confirmation is required during the trial, repeated 'non-measurable' time points will complicate the assessment of the best efficacy. The analysis plan of the trial must clarify how these missing data/evaluations can be interpreted when determining efficacy. For example, in most trials, a subject's response of PR-NE-PR can be considered as confirmation of efficacy.

When a subject experiences an overall deterioration in health that necessitates stopping treatment, but there is no objective evidence to support this, it should be reported as symptomatic progression. Efforts should still be made to assess objective progression even after treatment has been discontinued. Symptomatic deterioration is not a description of objective response assessment: it is the reason for stopping treatment. The objective response of such subjects will be assessed through the conditions of target and non-target lesions as shown in Appendices 1 to 3.

Conditions defined as early progression, early death, and unassessable situations are exceptions in the study and should be clearly described in each protocol (depending on the treatment interval and treatment cycle).

In some cases, it is difficult to distinguish local lesions from normal tissue. When the assessment of complete response is based on such definitions, we recommend performing a biopsy prior to the efficacy evaluation of complete response in local lesions. When some subjects have abnormal imaging results of local lesions that are considered indicative of lesion fibrosis or scar formation, FDG-PET is used as an assessment standard similar to biopsy for confirming complete response. In this case, the application of FDG-PET should be prospectively described in the protocol, supported by reports from specialized medical literature addressing this situation. However, it must be recognized that the inherent limitations of both FDG-PET and biopsy (including the varying resolutions and sensitivities of the two) will lead to false positive results in the assessment of complete response.

**Appendix 1 Time Point Response: Subjects with Target Lesions (Including or Excluding Non-Target Lesions)**

| **Target Lesion** | **Non-Target Lesion** | **New Lesion** | **Overall Response** |
| --- | --- | --- | --- |
| CR | CR | Non | CR |
| CR | Non-CR/Non-Disease Progression | Non | PR |
| CR | Not Assessable | Non | PR |
| PR | Non-Progression or Not Fully Assessable | Non | PR |
| SD | Non-Progression or Not Fully Assessable | Non | SD |
| Not Fully Assessable | Non-Progression | Non | NE |
| Disease Progression | Any Situation | Yes or No | Disease Progression |
| Any Situation | Disease Progression | Yes or No | Disease Progression |
| Any Situation | Any Situation | Yes | Disease Progression |
| CR = Complete Response | PR = Partial Response | SD = Stable Disease | NE = Not Evaluated |

**Table 2 Time Point Response - Subjects with Non-Target Lesions Only**

| **Non-Target Lesion** | **New Lesion** | **Overall Response** |
| --- | --- | --- |
| CR | Non | CR |
| Non-CR or non-disease progression | Non | Non-CR or Non-Disease Progression |
| Not Fully Assessable | Non | Not Assessable |
| Unclear Disease Progression | Yes or No | Disease Progression |
| Any Situation | Yes | Disease Progression |

Note: For non-target lesions, 'Non-CR/Non-Disease Progression' refers to efficacy better than SD. As SD is increasingly used as an endpoint for evaluating efficacy, the efficacy of Non-CR/Non-Disease Progression has been established to address situations where no measurable lesions are defined.

For unclear progression findings (such as very small uncertain new lesions; Treatment for cystic changes or necrotic lesions of the existing lesions can continue until the next evaluation. If disease progression is confirmed at the next evaluation, the date of progression should be the date when suspected progression first occurred.

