# Study Population

## Inclusion criteria

Patients who meet all of the following criteria may be included in this study:

1. Voluntary enrollment with signed written informed consent;
2. Aged 18 to 80 years (inclusive), regardless of gender;
3. Patients with hepatocellular carcinoma clinically diagnosed according to the 'Guidelines for the Diagnosis and Treatment of Primary Liver Cancer (2019 Edition)' or confirmed by histological/cytological diagnosis;
4. Patients with unresectable or metastatic hepatocellular carcinoma;
5. No prior systemic treatment. Patients who have received adjuvant chemotherapy after local treatment may also be included if the chemotherapy ended more than 12 months ago and there has been disease progression or metastasis;
6. The last intervention, radiotherapy, and ablation treatment must have ended more than 4 weeks ago;
7. Patients who have previously undergone liver resection should have R0 resection, and tumor recurrence should occur more than 24 months after surgery;
8. There must be at least one assessable lesion (according to RECIST 1.1 criteria) ;
9. Expected survival time ≥ 3 months;
10. Eastern Cooperative Oncology Group (ECOG) performance status (PS) score of 0-1;
11. Child-Pugh score ≤ 7;
12. Able to cooperate in observing adverse events and efficacy;
13. Major organ functions are normal, meeting the following criteria:

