**4. Tumor Efficacy Assessment**

**4.1 Assessment of All Tumors and Measurable Lesions**

To evaluate objective response or potential future progression, it is necessary to conduct a baseline assessment of the total tumor burden for all tumor lesions, serving as a reference for subsequent measurement results. In clinical protocols where objective response is the primary treatment endpoint, only patients with measurable lesions at baseline are eligible for inclusion. Measurable lesions are defined as the presence of at least one measurable lesion. For trials where disease progression (time to progression or degree of progression at a fixed date) is the primary treatment endpoint, the inclusion criteria must clearly specify whether it is limited to patients with measurable lesions or if patients without measurable lesions can also be included.

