**4.3.3 Assessment of Non-target Lesions**

This section defines the criteria for the response of non-target lesions. Although some non-target lesions are actually measurable, measurement is not required; qualitative assessment at the time points specified in the protocol is sufficient.

Complete Response (CR): All non-target lesions disappear, and tumor markers return to normal levels. All lymph nodes are of non-pathological size (short axis < 10 mm).

Partial Response (non-CR)/Stable Disease: One or more non-target lesions are present and/or tumor marker levels remain above normal.

Disease Progression: Existing non-target lesions show clear progression. Note: The appearance of one or more new lesions is also considered disease progression.

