**4.3.4 Special Considerations for the Assessment of Non-Target Lesion Progression**

The following is a supplementary explanation regarding the definition of progression of non-target lesions: When a patient has measurable non-target lesions, even if the target lesions are assessed as stable or partially responding, a clear definition of progression based on the non-target lesions must meet the criterion that the overall deterioration of the non-target lesions has reached a level that necessitates the termination of treatment. Moreover, a general increase in the size of one or more non-target lesions is often insufficient to meet the criteria for progression; therefore, in cases where the target lesions are stable or partially responding, it is exceedingly rare to define overall tumor progression solely based on changes in non-target lesions.

When all non-target lesions of the patient are unmeasurable: This situation may occur in some Phase III trials when the inclusion criteria do not specify that measurable lesions must be present. Overall assessment still refers to the above standards, but there are no measurable data for lesions in this situation. The deterioration of non-target lesions is not easy to assess (by definition: all non-target lesions must indeed be unmeasurable). Therefore, when changes in non-target lesions lead to an increase in overall disease burden equivalent to the progression of target lesions, a clear definition of progression based on non-target lesions requires the establishment of an effective detection method for evaluation. For example, an increase in tumor burden is described as a volume increase of 73% (equivalent to a 20% increase in the diameter of measurable lesions). Additionally, peritoneal effusion may range from 'trace' to 'massive'; lymphatic involvement may progress from 'localized' to 'widely disseminated'; or it may be described in the protocol as 'sufficient to necessitate a change in treatment approach.'Examples include pleural effusion ranging from trace to massive, lymphatic involvement spreading from the primary site to distant sites, or it may be described in the protocol as 'necessitating a change in treatment.'If clear progression is observed, the patient should be considered to have disease progression at that point overall. It is best to have objective criteria applicable to the assessment of unmeasurable lesions; note that the additional criteria must be reliable.

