In some cases, it is difficult to distinguish local lesions from normal tissue. When the assessment of complete response is based on such definitions, we recommend performing a biopsy prior to the efficacy evaluation of complete response in local lesions. When some subjects have abnormal imaging results of local lesions that are considered indicative of lesion fibrosis or scar formation, FDG-PET is used as an assessment standard similar to biopsy for confirming complete response. In this case, the application of FDG-PET should be prospectively described in the protocol, supported by reports from specialized medical literature addressing this situation. However, it must be recognized that the inherent limitations of both FDG-PET and biopsy (including the varying resolutions and sensitivities of the two) will lead to false positive results in the assessment of complete response.

Table 1 Response at Time Points: Subjects with Target Lesions (including or excluding non-target lesions)

| Target Lesion | Non-Target Lesion | New Lesion | Overall Response |
| --- | --- | --- | --- |
| CR | CR | Non | CR |
| CR | Non-CR/Non-PD | Non | PR |
| CR | Not Assessable | Non | PR |
| PR | Non-Progression or Not Fully Assessable | Non | PR |
| SD | Non-Progression or Not Fully Assessable | Non | SD |
| Not Fully Assessable | Non-Progression | Non | NE |
| PD | Any Situation | Yes or No | PD |
| Any Situation | PD | Yes or No | PD |
| Any Situation | Any Situation | Yes | PD |
| CR = Complete Response | PR = Partial Response | SD = Stable Disease | PD = Progressive Disease  NE = Not Evaluated |

Table 2 Response at Time Points - Subjects with Only Non-Target Lesions

| Non-Target Lesion | New Lesion | Overall Response |
| --- | --- | --- |
| CR | Non | CR |
| Non-CR or non-PD | Non | Non-CR or Non-PD |
| Not Fully Assessable | Non | Not Assessable |
| Unclear PD | Yes or No | PD |
| Any Situation | Yes | PD |

Note: For non-target lesions, 'Non-CR/Non-PD' refers to efficacy superior to SD. As SD is increasingly used as an endpoint for evaluating efficacy, the definition of Non-CR/Non-PD efficacy is established to address situations where no measurable lesions are specified.

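### In both response appendices the table for patients with only non-target lesions scores unclear progression as PD, against the appendices' own clear-progression rule and the note after each table

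*Protocol*

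**What the plan says.** **The table rows.** Appendix II (RECIST v1.1), Table 2, for subjects with only non-target lesions: "Unclear Disease Progression | Yes or No | Disease Progression". The corresponding table in Appendix III (mRECIST), placed after its section 4.4.4: "Unclear PD | Yes or No | PD". The columns are non-target status, new lesion and overall response.

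**The text rule.** Section 4.3.3 of Appendix II defines the non-target category as "Disease Progression: Existing non-target lesions show clear progression", and section 4.3.3 of Appendix III says the same. Section 4.3.4 of each appendix covers patients whose non-target disease is all unmeasurable: "If clear progression is observed, the patient should be considered to have disease progression at that point overall".

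**The note after each table.** For unclear findings, such as a very small doubtful new lesion or cystic or necrotic change, treatment may go on to the next evaluation. Then: "If disease progression is confirmed at the next evaluation, the date of progression should be the date when suspected progression first occurred".

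**Who can reach this table.** Inclusion criterion 8 reads "There must be at least one assessable lesion (according to RECIST 1.1 criteria". Section 4.1 of both appendices says that, where objective response is the primary endpoint, "only patients with measurable lesions at baseline are eligible for inclusion". ORR is the primary endpoint here.

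**The concern.** The row gives the opposite of the rule it should implement. The one situation that the text defines as progression, clear worsening without a new lesion, cannot be looked up. The situation that the note tells readers to hold over is called PD at once.

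PFS, TTP and DCR are secondary endpoints built on these calls. Trial treatment stops on imaging progression that meets RECIST v1.1 and mRECIST together, and one might expect that double requirement to filter out a doubtful call. It cannot do so here, because both tables carry the same wording. Images are read at the single centre (section 9.3), so these tables are working instructions for the people who make the call.

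**Working it through.** The plan gives no figure to reproduce: section 3.2 fixes 30 patients without a derivation. The check is a comparison of the rules.

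**Step 1. A patient with only non-target lesions and no new lesion.**

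| Finding at a scan | Table row read literally | Text (4.3.3, 4.3.4) and note |
|---|---|---|
| Clear progression | No matching row | PD at that scan |
| Unclear, confirmed at the next evaluation | PD at the first scan | PD, dated to the first scan |
| Unclear, never confirmed | PD at the first scan | No progression event |

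The second line gives the same event date under both readings. Only the third changes an endpoint. The first is a gap that a reader would probably fill from the text.

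**Step 2. Is the wording used elsewhere?** In both appendices, Table 1, for patients with target lesions, gives the non-target entry as plain progression, without *unclear*. The problem is confined to the non-target-only tables.

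**Step 3. Can such patients be enrolled?** Criterion 8 asks for an assessable lesion, not a measurable one. Criterion 6 admits patients more than 4 weeks after interventional treatment, radiotherapy or ablation. Section 3.1.3 of both appendices regards locally treated lesions as generally non-measurable unless they are shown to be still active or progressing, and asks the protocol to state when they count as measurable. The main protocol sections do not do so. The route is therefore open under criterion 8 and closed under section 4.1 of the appendices.

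**Step 4. Size per patient.** 1/30 = 0.033, so one miscalled patient moves a landmark PFS or progression-free proportion by at most 3.3 percentage points.

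**Step 5. Range under assumptions.** The documents give neither the share of non-target-only patients nor the rate of equivocal findings that are never confirmed. For illustration only, assume shares of 5% to 15% and rates of 5% to 20% among those patients:

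- Probability per enrolled patient: 0.05 × 0.05 = 0.0025 to 0.15 × 0.20 = 0.03.
- Expected miscalls among 30: 30 × 0.0025 = 0.08 to 30 × 0.03 = 0.9.
- Chance of at least one: 1 − 0.9975^30 = 7% to 1 − 0.97^30 = 60%.

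These figures also suppose that readers follow the row and disregard the note. If measurable disease is enforced at entry, all of them are zero.

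**The case against.** The strongest reply is that the document already contains the right handling. The note stands directly after each table, the text asks for clear progression, section 7.4.1 dates PFS at the first progression confirmed on imaging, and section 7.4.3 ties TTP to objective progression. Both appendices call themselves internal translations and send the reader to the English version, so a translation slip is the likely cause. Most of this stands. It shows that a careful reader would avoid the error, but not that the row is right. A table and its own note give opposite instructions, and neither 7.4.1 nor 7.4.3 asks for a repeat scan.

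A reader might also draw stronger conclusions that the documents do not support:

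- *That equivocal findings will become PFS and TTP events.* This follows only if the row is read alone and the finding is never confirmed.
- *That the appendices' remark on how rarely non-target change alone defines progression adds support.* That remark concerns patients whose target lesions are stable or responding, who are not in this table. The sentence on clear progression in 4.3.4 is the relevant one.
- *That a miscall is nearly certain.* With an assumed 5% to 15% share, 1 − 0.95^30 = 79% and 1 − 0.85^30 = 99%. These are chances of enrolling at least one non-target-only patient, not of miscalling one.
- *That DOR is materially affected.* DOR exists only for responders, and the only response available in this table is CR.
- *That a false call could not be repaired.* Scheduled scanning stops only once progression is confirmed, and nothing in the protocol prevents the centre from re-reading its images.

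**Conclusion.** The contradiction is certain: in both appendices one row conflicts with the clear-progression rule and with the note that follows it. It is a minor wording error with a conditional effect.

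An endpoint changes only if all of the following occur: a patient without target lesions is enrolled, an equivocal non-target finding arises and is never confirmed, and the reader applies the row rather than the note. PFS and TTP would then gain a false event, and best response and DCR might record a false PD. The number of such patients is not given and may be zero. Each would be 1 of 30, or 3.3 percentage points, on secondary descriptive endpoints. The primary ORR is essentially unaffected, since such a patient could count as a responder only through CR.

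**What to change.** In Appendix II, Table 2, and in the non-target-only table of Appendix III (the first of the two tables numbered 2 there), change the first cell of the row to clear (unequivocal) progression. Add a pointer from the table to the existing note, so that an unclear finding is not PD at that time point and, if confirmed at the next evaluation, is dated to the first suspicion. Table, text and note then agree.

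Separately, reconcile *assessable* in inclusion criterion 8 (protocol summary and section 4.1) with the measurable-lesion rule in section 4.1 of both appendices, so that it is clear whether non-target-only patients can be enrolled at all.

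The cost is one cell and one cross-reference in each appendix, plus the wording of one criterion in two places. The table correction needs no extra data or visits and is best made before scans are read against these tables.

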**Table 3: Best overall response requiring confirmation for CR and PR efficacy**

| **First time point overall response** | **Subsequent time point overall response** | **Best overall response** |
| --- | --- | --- |
| CR | CR | CR |
| CR | PR | SD, disease progression, or PR ^a^ |
| CR | SD | If SD persists for a sufficient duration, it is considered SD; otherwise, it should be classified as disease progression. |
| CR | Disease Progression | If SD persists for a sufficient duration, it is considered SD; otherwise, it should be classified as disease progression. |
| CR | NE | If SD persists for a sufficient duration, it is considered SD; otherwise, it should be classified as NE. |
| PR | CR | PR |
| PR | PR | PR |
| PR | SD | SD |
| PR | Disease Progression | If SD persists for a sufficient duration, it is considered SD; otherwise, it should be classified as disease progression. |
| PR | NE | If SD persists for a sufficient duration, it is considered SD; otherwise, it should be classified as NE. |
| NE | NE | NE |

Note: CR = Complete Response, PR = Partial Response, SD = Stable Disease; NE = Not Evaluated.

Superscript 'a': If a CR truly occurs at the first time point, any disease that appears at subsequent time points will result in the efficacy evaluation of that subject being classified as PD at later time points, even if the subject's efficacy reaches the PR standard relative to baseline (because the disease will reappear after CR). The best response depends on whether SD occurs within the shortest treatment interval. However, sometimes the first evaluation is CR, but subsequent scans suggest that small lesions still seem to appear, thus the actual efficacy of the subject at the first time point should be PR rather than CR. In this case, the initial CR judgment should be modified to PR, and the best response is PR.

**Frequency of tumor re-evaluation at 4.5**

The frequency of tumor re-evaluation during treatment is determined by the treatment regimen and should align with the type and schedule of the treatment. However, in Phase II trials where the benefit of treatment is unclear, it is reasonable to conduct follow-ups every 6 to 8 weeks (timed at the end point of a cycle), with adjustments to the interval length possible in special protocols or circumstances. The protocol should specifically indicate which tissue sites require baseline level assessments (typically those most likely to be closely related to metastatic lesions of the tumor type under investigation) and the frequency of repeated evaluations. Under normal circumstances, both target lesions and non-target lesions should be evaluated at each assessment. In certain selectable situations, the evaluation frequency of some non-target lesions may be reduced, for example, a repeat bone scan is only required when the efficacy evaluation of the target disease confirms CR or there is suspicion of progression in bone lesions.

The re-evaluation of the tumor after treatment depends on whether the response rate or the time to the occurrence of a specific event (progression/death) is used as the endpoint of the clinical trial. If the endpoint is the time to the occurrence of a specific event (e.g., TTP/DFS/PFS), then routine repeated evaluations as specified in the protocol are required. Especially in randomized comparative trials, the predetermined evaluations should be listed in the timetable (e.g., 6 to 8 weeks during treatment, or 3 to 4 months after treatment) and should not be influenced by other factors, such as treatment delays, administration intervals, and any other events that may lead to an imbalance in treatment arms regarding the timing of disease evaluation.

